**Discussion:**

We hypothesize that the physical activity-promoting culture will yield superior effects than either intervention alone on the primary outcomes. Furthermore, both the guided environmental intervention and the exercise intervention are expected to be more effective than the non-guided environmental intervention. We aim to encourage nursing home residents to actively participate in social life and to derive guidelines for health promotion.

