### Statistical analysis

The descriptive statistics will be presented as either group mean values and standard deviations/errors or medians and interquartile ranges, depending on the distribution of the outcome measures. The intervention effect for the primary outcomes (Number of Steps and SPPB) will be analyzed separately using a 4 (between group: PA-promoting culture intervention, guided environmental intervention, non-guided environmental intervention, or exercise intervention) × 2 (within test time point: t1:t2, and t2:t3) linear mixed model, where participants can be nested within nursing homes and be calculated as a random effect. The Follow-Up effects will be analyzed additionally using a 4 (between group: all interventions) x 3 (within test timepoint: t1/t2 – t2/t3 – t4). If baseline differences are found, the baseline assessment values, as well as age and sex discrepancies, will be included as covariates in the statistical model. In cases of statistically significant interaction effects, Bonferroni-adjusted *post hoc* tests (such as t-tests or Wilcoxon tests) will be employed to identify significant differences between groups from baseline to post-allocation testing. The data will be pre-processed and analysed using SPSS.

The effect size will be determined using Cohen’s f, which indicates the magnitude of treatment effectiveness and helps assess whether a statistically significant difference is practically significant (Cohen and Ebl, 1988). Cohen’s f values are classified as small (0 ≤ f ≤ 0.24), medium (0.25 ≤ f ≤ 0.39), or large (f ≥ 0.40) (Grissom and Kim, 2011). For *post hoc* analysis, Cohen’s d effect size will be calculated. Additionally, PSdep scores (probability of superiority for dependent samples) will be calculated as an estimate of effect size in non-parametric *post hoc* tests. The significance level will be set at p < 0.05. An intention-to-treat analysis will be conducted, considering all participants in the groups to which they were randomly assigned, regardless of whether they received or adhered to the assigned intervention. We will control participation in the interventions to analyze the effect of the intervention in more detail. Multiple imputations will be used to handle missing data, assuming that the missingness is random. If more than 40% of participants are lost to outcome assessment or demonstrate insufficient participation in training sessions, an additional per-protocol analysis will be conducted.

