### Sample size estimate/power calculations

Statistical power analysis was conducted to estimate the sample size to test our hypothesis in G*Power (Version 3.1.9.4, Heinrich Heine University of Duesseldorf) (Faul et al., 2009). The following input parameters were used to obtain small-sized test × group interaction effects within an ANOVA: effect size (*f* = 0.15) (i.e., a small effect, (Tudor-Locke et al., 2011), type I error (α = 0.025), type II error (1-β = 0.8), number of groups (n = 4), number of measurements (n = 2), correlation between measurements (r = 0.60).

The size of the estimated sample to generate sufficient power to achieve the small effect is N = 88. To compensate for the estimated dropout rate of 30% (e.g., 20% lost to follow-up; plus 10% mortality) we plan to include a total of N = 116 participants. Based on the study design, we will integrate N = 29 participants in each condition.

Regarding the special cohort, recruiting approximately 30 participants per intervention arm per nursing home seems unrealistic, so multiple nursing homes will be needed for each intervention arm. As the number of nursing homes is also limited, each one needs to take on more than one intervention arm to reach a total of ∼30 participants. By the life expectancy of the special cohort and for ethical reasons, we have limited the maximum study duration to 1 year per participant. This means that each participant can complete two intervention phases and one follow-up phase per year, nested in a nursing home. In terms of the four intervention arms, this means six different possible combinations (this means six different nursing homes), each with 10–20 nursing home residents participating in the study.

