## Discussion

This cluster-randomized trial aims to assess the impact of a physical activity-promoting culture, compared to three other interventions, on nursing home residents’ PA behavior and physical functioning. We expect the physical activity-promoting culture, which combines exercise classes and environmental changes, to increase PA, reduce sedentary behavior, and improve physical functioning (Giurgiu et al., 2020; Lopponen et al., 2021) more effectively than either intervention alone or a non-guided environmental intervention. Overall, the PROGRESS study offers a new practical approach to implementing active aging in nursing homes. It aims to encourage the integration of PA programs led by professionally educated instructors into the prevention planning of nursing homes, together with environmental changes that might promote PA behavior in general. The participatory approach enables residents, nursing staff, social services, and relatives to be aware of and incorporate any changes in the residents’ environment. This approach is hypothesized to promote physical functioning and activity, even in challenging situations. A physical activity-promoting culture that is lively, happy, and healthy can only be developed if all individuals who work, live, and visit the nursing home support each other through PA. The findings can provide guidance for addressing current and future challenges in health promotion initiatives in long-term care, which is of great importance in aging societies.

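### The five stated group comparisons are reached only as Bonferroni post hoc tests after an omnibus interaction, and the 80% power target belongs to that interaction, not to any of them

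*Protocol article*

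**What the plan says.** The hypotheses are pairwise and directional. The Discussion paragraph of the Abstract states: "We hypothesize that the physical activity-promoting culture will yield superior effects than either intervention alone on the primary outcomes". It adds that "both the guided environmental intervention and the exercise intervention are expected to be more effective than the non-guided environmental intervention". The last paragraph of the Introduction repeats both. That gives four comparisons: combined vs exercise, combined vs guided, exercise vs non-guided, guided vs non-guided. The main Discussion adds a fifth, combined vs non-guided, by expecting the combined arm to work "more effectively than either intervention alone or a non-guided environmental intervention".

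The Statistical analysis section fits a 4 × 2 linear mixed model to each primary outcome (steps per day and SPPB). It compares groups only under a condition: "In cases of statistically significant interaction effects, Bonferroni-adjusted" post hoc tests are then used, with t-tests or Wilcoxon tests as examples. No planned contrast is named, and neither the number of pairs in the Bonferroni family nor the sidedness is given. The significance level is 0.05.

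The Sample size estimate/power calculations section opens: "Statistical power analysis was conducted to estimate the sample size to test our hypothesis in G*Power". Its inputs are chosen "to obtain small-sized test × group interaction effects within an ANOVA", with "effect size (*f* = 0.15", "type I error (α = 0.025), type II error (1-β = 0.8", four groups, two measurements and r = 0.60. It reports N = 88 before dropout and N = 116 planned.

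**The concern.** The hypotheses, the test procedure and the power statement address different questions. The hypotheses are about named pairs. The procedure first asks whether the four arms differ in any way, and then treats the named pairs as post hoc. The power statement covers the first question but is worded as if it covered the second.

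This has two consequences. A reader will take 80% as the chance of showing that the combined arm beats each of its components, which was never calculated. The analysis also adjusts the stated comparisons by a single-step method that may include a pair with no stated hypothesis (exercise vs guided), although a step-down method over the stated pairs gives the same familywise protection with more power. Because Bonferroni already controls the familywise error, the omnibus gate in front of it adds no needed protection.

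**Working it through.** **1. The protocol's own figure.** For a within-between interaction, λ = f²·N·m/(1 − r), with df (k − 1)(m − 1) and (N − k)(m − 1). The inputs are f = 0.15, m = 2, r = 0.60, k = 4 and α = 0.025.

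- N = 88: λ = 0.0225 × 88 × 2/0.40 = 9.9, df 3 and 84, power 63.1% (73.5% at α = 0.05).
- N = 116: λ = 13.05, power 78.5%.
- N = 120: λ = 13.5, power 80.2%.

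So the stated inputs need N = 120 for 80%, and 88 is not reproduced. At α = 0.05 the need is 104. A run with 2 groups × 2 measurements returns 80.5% at N = 88, but that is not the stated design.

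**2. From f to a pairwise difference.** With two time points, f = 0.15 means that the SD of the four group mean changes is 2 × 0.15 = 0.30σ. The SD of an individual change is σ√(2(1 − 0.60)) = 0.894σ, so f on the change scale is 0.30/0.894 = 0.335. As a check, 0.335² × 88 ≈ 9.9, the λ above.

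Assume equal steps in the hypothesised order: combined = a, exercise = guided = 0, non-guided = −a. The SD of these means is a/√2, so a = 0.335 × √2 = 0.474 change-SD. Four of the five contrasts equal a (one step). Combined vs non-guided equals 2a = 0.95.

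**3. Numbers per arm.** Without counting the crossover: 88/4 = 22. Each resident completes two phases, so 88 × 2/4 = 44 resident-phases per arm. With all enrolled residents, 116 × 2/4 = 58.

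**4. Power for one step.** The non-centrality is 0.474·√(n/2) with 4n − 4 df: 1.57 at n = 22, 2.22 at 44 and 2.55 at 58. At two-sided 0.05/6 this gives 13.6%, 33.1% and 45.9%. Simulation gave the gated, Holm and joint figures. All are at α = 0.05 with independent normal change scores.

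| n per arm | One step: gated Bonferroni over 6 | One step: ungated Holm over 5 | Both combined-vs-component contrasts: gated Bonferroni over 6 | Both: ungated Holm over 5 |
|---|---|---|---|---|
| 22 | 14% | 19% | 5% | 10% |
| 44 | 33% | 45% | 18% | 32% |
| 58 | 46% | 61% | 29% | 48% |

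**5. What the gate costs.** Bonferroni over six without the gate gives 13.8% at n = 22 and 46.1% at n = 58, the same as with it. Across the contrasts examined, the gate costs 0 to 2 points.

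**6. Sensitivity.**

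- *Family size:* if the Bonferroni family were four pairs, gated power for one step would be 17%, 38% and 52% at 22, 44 and 58, so part of the gain from Holm disappears.
- *Alpha:* at 0.025 with six pairs, single-step power is 9.2%, 25.2% and 36.9%.
- *Pattern of means:* if only the combined arm differs, at the same f, each combined-arm contrast has about 83% at 44 per arm under the plan (α = 0.05, six pairs). The two hypotheses against non-guided would then be false. Equally spaced means (3, 2, 1, 0) make the adjacent differences smaller (0.30 change-SD) and their power lower.

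**The case against.** The strongest reply is that the gate does almost no harm. A pair that passes 0.05/6 nearly always comes with a significant omnibus test, so the choice is between two valid procedures, and naming the contrast family is commonly left to an analysis plan that is not shown here. Much of this stands. A reader might infer that the gate leaves the hypotheses effectively untested or takes much of the power; step 5 shows that it does not. Nor does the plan inflate the familywise error within an outcome. An unstated family size alone would be no finding. What remains is what the article does fix: a procedure that treats its stated hypotheses as post hoc, and a power claim worded for those hypotheses but calculated for something else.

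A reader might also infer that no stated comparison can reach 80%. The documents do not support that. Under equal steps, combined vs non-guided has 66% at 22 per arm, 81% at 29 (116/4) and 99% at 58 under the plan, and step 6 gives a pattern in which the combined-arm contrasts exceed 80% at 44. For the same reason it would be wrong to call combined vs non-guided an unplanned pair: the main Discussion states it. Only exercise vs guided has no stated direction.

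Finally, 22 per arm ignores the two phases per resident, so 44 is the fairer reading of N = 88. Within-resident comparisons in the crossover could raise power for some pairs; clustering in six homes would probably lower it. Neither is in these figures.

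**Conclusion.** The point holds in this form: five directional comparisons are stated, none is a planned test, and the 80% was set for the omnibus interaction. It is not the power of any of the five, though some may reach it under some patterns of means.

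Replacing gated Bonferroni over six with ungated Holm over the five raises power for a one-step comparison by about 5 points at 22 per arm, 12 at 44 and 15 at 58. For both combined-vs-component contrasts the gain is about 5, 14 and 19 points. The gain comes from the step-down method and the smaller family, hardly at all from removing the gate. These sizes assume f = 0.15, r = 0.60, equal steps, two-sided 0.05, a six-pair family, and no clustering or pairing. With a four-pair family the gain is smaller.

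The 80% is also not what the stated inputs return for the interaction (63% at N = 88). That is a check of the calculation as written, not a forecast for the trial: counting two phases per resident as independent (44 per arm) would put the interaction at about 95% at α = 0.025. Even then, one-step contrasts under equal steps stay well below 80%. With single-step Bonferroni at 0.05, 80% would need about 100 (four pairs) or 108 (six pairs) per arm.

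**What to change.** - **Statistical analysis section:** name the five stated contrasts as the confirmatory tests for each primary outcome. Estimate them from the mixed model, so that the nursing-home structure is kept, and test them whatever the omnibus result, with Holm over five. Report the omnibus interaction and exercise vs guided descriptively.
- **Sample size section:** say that 80% was the target for the omnibus interaction, and correct it (63% at N = 88 with the stated inputs; N = 120 for 80%). Report power for the named contrasts with the assumed pattern of means, at one alpha that agrees with the analysis section; at present it is 0.025 in one place and 0.05 in the other.

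This changes wording and analysis only. It needs no new residents, visits or data, and familywise control within each outcome is kept. It is most credible if fixed before outcomes are analysed. The costs are that exercise vs guided is no longer confirmatory and that the stated power becomes less favourable. Keeping combined vs non-guided in the family costs almost nothing: at 22 per arm, Holm over five gives 18.7% per one-step contrast against 19.0% over four, and at 58 per arm 61.0% against 61.0%.

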**Methods:**

The study employs a cluster-randomized controlled crossover design with four intervention groups. Participants will be randomly assigned to one of four groups: a combined exercise and guided environmental intervention (physical activity-promoting culture), an exercise intervention, a guided environmental intervention, or a non-guided environmental intervention. The exercise intervention involves group-based sessions twice a week, while the environmental intervention focuses on implementing PA into daily routines. The guided environmental intervention is equivalent to the non-guided one but provides additional support two to four times weekly. We aim to recruit at least 120 participants from six nursing homes. Each facility will receive two interventions in a 16-week crossover design (36 weeks in total, including weeks for measurements), followed by a 16-week non-guided environmental intervention (follow-up phase). Primary outcomes include steps per day as an indicator of PA behavior, and the Short Physical Performance Battery (SPPB) to assess physical functioning.

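### The sample size is set at α = 0.025, but the two primary outcomes are to be tested separately at p < 0.05 with no rule across them; the two levels contradict each other.

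*Protocol article*

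**What the plan says.** The abstract names two primary outcomes: "Primary outcomes include steps per day as an indicator of PA behavior, and the Short Physical Performance Battery (SPPB) to assess physical functioning". The Statistical analysis section gives each its own model: "The intervention effect for the primary outcomes (Number of Steps and SPPB) will be analyzed separately". The significance level appears once there, with no exception for the primary outcomes: "The significance level will be set at p < 0.05".

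The only multiplicity step in that section follows a positive interaction test and concerns comparisons between groups: "In cases of statistically significant interaction effects, Bonferroni-adjusted *post hoc* tests (such as t-tests or Wilcoxon tests) will be employed".

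The Sample size section powers the interaction F test ("The following input parameters were used to obtain small-sized test × group interaction effects within an ANOVA") with the inputs "type I error (α = 0.025), type II error (1-β = 0.8), number of groups (n = 4), number of measurements (n = 2), correlation between measurements (r = 0.60" and f = 0.15. It gives no reason for 0.025. Neither section orders the two outcomes, divides the error between them, or requires both to be significant.

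**The concern.** The interaction test sized in one section is the test that opens the primary analysis in the other, so one level should govern both. As printed, there are two. A primary interaction with p = 0.03 would be called significant under Statistical analysis and would miss the level on which the trial was sized.

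Two things are at stake. The first is the error rate of the primary claim: two separate tests at 0.05 exceed 5% in total if success on either one counts. The second is credibility, because a choice between 0.025 and 0.05 made after the results are known would be open to challenge.

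**Working it through.** **1. Was 0.025 really used for the sizing?** Inputs from the Sample size section: f = 0.15, k = 4 groups, m = 2 measurements, r = 0.60, power 0.80, stated N = 88. For the repeated-measures F test, λ = f²·N·m/(1 − r), with denominator df = (N − k)(m − 1). At N = 88, λ = 0.0225 × 88 × 2/0.40 = 9.9, with 84 denominator df.

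| Test | α | N needed for 80% | Power at N = 88 |
|---|---|---|---|
| 4-group × 2-time interaction (3 df), as stated | 0.05 | 101 | 73.5% |
| same | 0.025 | 120 | 63.1% |
| 1-df effect (e.g. time main effect) | 0.05 | 72 | 87.5% |
| same | 0.025 | **88** | 80.4% |

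The stated interaction does not give 88 at either level. Among the variants tried, 88 comes out only at 0.025 with 1 df. So 0.025 appears to have been entered and is probably not a misprint. That 88 does not fit the stated interaction is a separate problem; it matters here only for the cost of the fix.

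**2. Error across the two interaction tests, if either suffices.**
- Each at 0.05, independent: 1 − 0.95² = 0.0975. Upper bound under any dependence: 0.05 + 0.05 = 0.10.
- Each at 0.025, independent: 1 − 0.975² = 0.0494. Upper bound: 0.025 + 0.025 = 0.05.

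The article gives no correlation between the outcomes, so a range is assumed. Simulation of two correlated 3-df F tests (four groups of 29, normal data, 200,000 runs):

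| Assumed correlation | Each at 0.05 | Each at 0.025 |
|---|---|---|
| 0 | 9.7% | 4.9% |
| 0.5 | 9.2% | 4.7% |
| 0.7 | 8.4% | 4.4% |
| 0.9 | 7.1% | 3.6% |

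**3. Error for a pairwise claim.** The hypotheses compare one intervention with another, so a false claim needs a significant interaction and then a significant Bonferroni-adjusted contrast. Same simulation, all groups equal on both outcomes, six two-sample t-tests each at 0.05/6, either outcome sufficient:

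| Assumed correlation | Any false pairwise claim, level 0.05 |
|---|---|
| 0 | 6.8% |
| 0.5 | 6.4% |
| 0.7 | 6.0% |

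Using the pooled variance in the contrasts gives 7.4%, 7.0% and 6.5%. Both simulations treat the groups as independent and ignore clustering and the crossover.

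**The case against.** The strongest defence is that the authors probably meant to control the error. An F test has no one-sided half, so 0.025 reads most naturally as 0.05 shared between two outcomes, and the 0.05 in Statistical analysis may simply be the overall level. This is plausible, but it is an inference: a reader might conclude that the Sample size section splits alpha, and that section neither says so nor mentions two outcomes. If the inference is right, the analysis section still needs a correction, because it attaches 0.05 to the separate tests without qualification.

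A second defence is that the hypotheses speak of the primary outcomes in the plural. If both had to be significant, testing each at 0.05 would inflate nothing. This stands as a possible reading, but no such rule is stated, and it would leave 0.025 unexplained.

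A third is that the Bonferroni step protects the claims that matter. It does so in part: it brings the excess for pairwise claims down to about 6 to 7%. It works within one outcome after the interaction test, so it does not remove the excess across outcomes.

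Finally, allocation of alpha is often left to a statistical analysis plan, which is not at hand. That would excuse silence. It does not excuse two printed levels that disagree.

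**Conclusion.** The contradiction stands on the text alone, whatever the reason for 0.025. It needs correcting before analysis because it decides whether a primary result counts as positive.

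The inflation is conditional on success on either outcome being enough, which the article does not say. Under that assumption, the chance of at least one false significant interaction is at most 9.75% for independent outcomes and lower with positive correlation. The chance of a false pairwise claim is about 6 to 7% under a global null; partial nulls could differ.

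A reader might infer that the false-positive rate of the primary claim is nearly doubled. The article does not support that as a flat statement: it describes the omnibus tests at low to moderate correlation under an either-outcome rule, not the pairwise claims after adjustment. A reader might also infer that the stricter level costs nothing because the trial was sized on it. With the stated inputs that is not so, since the four-group interaction has about 63% power at N = 88 and α = 0.025.

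**What to change.** Choose one rule and state it in Statistical analysis.

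- **Either outcome suffices:** test the interaction for each primary outcome at α = 0.025, or use Holm across the two (smaller p-value against 0.025 and, if that succeeds, the other against 0.05). Adjust the post hoc contrasts from the level at which that outcome was tested. Do not call the level two-sided, since a 3-df F test has no sides.
- **Both must be significant:** say so, keep 0.05 for each, and change the Sample size section to match.

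The wording is a sentence or two. The cost is power, and the power statement should be redone for the level chosen. With the stated inputs at N = 88, the interaction has about 63% power at 0.025 against 73% at 0.05, a loss of about 10 percentage points per outcome; Holm recovers part of this when the first test succeeds. If both must succeed, and the effect is f = 0.15 on each, joint power at 0.05 lies between 0.735² = 54% (independent outcomes) and 73% (perfect correlation).
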